### **9.4.2 Pregnancy Test**

At Day 0 (treatment day with Rhenium-SCT), urine samples will be analysed for Human Chorionic Gonadotropin (hCG) to assess pregnancy status in females of childbearing potential. All women, including those with tubal ligation, are considered to be of childbearing potential unless they have been postmenopausal for at least 2 years. Hysterectomized women are considered surgically sterile.

### **9.4.3 Pharmacokinetics**

No pharmacokinetic evaluations are planned (Rhenium-SCT is administered by application on a protective foil applied over the area to be treated, such that the radioactive material does not come into contact with the subject).

### **9.4.4 Pharmacodynamics**

No pharmacodynamic evaluations are planned (Rhenium-SCT is administered by application on a protective foil applied over the area to be treated, such that the radioactive material does not come into contact with the subject).

### **9.4.5 Pharmacogenetics**

No pharmacogenetic evaluations are planned (Rhenium-SCT is administered by application on a protective foil applied over the area to be treated, such that the radioactive material does not come into contact with the subject).

## 10. PHARMACOVIGILANCE

### 10.1 Definition of Adverse Events

An AE is defined as any untoward medical occurrence in a subject administered a treatment and which does not necessarily have a causal relationship with this treatment. An AE can therefore be any new sign, symptom, illness, or syndrome, any abnormal laboratory values, if judged clinically significant in the opinion of the investigator, any worsening (change in nature, severity or frequency) of a concomitant or pre-existing illness, any adverse effect of the investigational medicinal product/device, including comparator or concomitant medication, any product/device interactions, any adverse effect of an invasive procedure required by the protocol or any accident or injury, whether or not related to the investigational medicinal product/device.

All AEs fall into one of two categories: “non-serious” and “serious”.

In this study, the following medical events will not be considered to fall under the definition of an AE:

- Surgical procedures or other therapeutic interventions themselves are not AEs, but the condition for which the surgery/intervention is required is an AE and should be documented accordingly.
- Planned surgical measures and the condition(s) leading to these measures are not AEs, if the condition(s) was (were) known before the period of observation and did not worsen during study. In the latter case, the condition should be reported as medical history.
- Any SAEs detected by the investigator in a study subject after the end of the period of observation, which the investigator does not consider to be related to prior study treatment or procedures

Progression of the cancer under study is not considered an AE unless it results in hospitalization or death.

The study will collect all AEs for the first 30 days of the study, after which only AE's deemed treatment (device) related will be collected.

### 10.2 Definition of Serious Adverse Events (SAEs)

An SAE is any untoward medical occurrence that at any dose (including overdose):

#### **Medical Device (MDR 2017/745)**

Serious adverse event is any adverse event that led to any of the following:

- a) death,
- b) serious deterioration in the health of the subject, that resulted in any of the following:
  - 1) life-threatening illness or injury,
  - 2) permanent impairment of a body structure or a body function,
  - 3) hospitalization or prolongation of patient hospitalization
  - 4) medical or surgical intervention to prevent life-threatening illness or injury or permanent impairment to a body structure or a body function,

- 5) chronic disease
- c) fetal distress, fetal death or a congenital physical or mental impairment or birth defect

NOTE 1 Planned hospitalization for a pre-existing condition, or a procedure required by the protocol, without serious deterioration in health, is not considered a serious adverse event.

Any adverse events that do not satisfy these descriptions are defined as being non-serious.

## **10.3 Definition for Medical Device**

### **10.3.1 Adverse Device Effect (ADE)**

Adverse event related to the use of an investigational medical device (ISO 14155:2020).

NOTE 1 This definition includes adverse events resulting from insufficient or inadequate instructions for use, deployment, implantation, installation, or operation, or any malfunction of the investigational medical device.

NOTE 2 This definition includes any event resulting from use error or from intentional misuse of the investigational medical device.

### **10.3.2 Device Deficiency (DD)**

An inadequacy of a medical device with respect to its identity, quality, durability, reliability, usability, safety or performance (ISO 14155:2020).

NOTE 1 Device deficiencies include malfunctions, use errors, and inadequacy in the information supplied by the manufacturer including labelling.

NOTE 2 This definition includes device deficiencies related to the investigational medical device or the comparator.

### **10.3.3 Incident and Serious Incident**

Incident means any malfunction or deterioration in the characteristics or performance of a device made available on the market, including use-error due to ergonomic features, as well as any inadequacy in the information supplied by the manufacturer and any undesirable side-effect (MDR 2017/745).

Serious incident means any incident that directly or indirectly led, might have led or might lead to any of the following:

- a) the death of a patient, user or other person,
- b) the temporary or permanent serious deterioration of a patient's, user's or other person's state of health,
- c) a serious public health threat (MDR 2017/745).

### **10.3.4 Unanticipated Serious Adverse Device Effect (USADE)**

A SADE which by its nature, incidence, severity or outcome has not been identified in the current version of the risk analysis report (ISO 14155:2020).

NOTE Anticipated serious adverse device effect (ASADE) is an effect which by its nature, incidence, severity or outcome has been identified in the risk analysis report.

## 10.4 Period of Observation

All AEs that occur after the consent form is signed but before treatment with investigational medicinal products/devices must be reported by the investigator if they cause the subject to be excluded from the study or are the result of a protocol-specified intervention.

For the purposes of this study, the period of observation for collection of AEs extends from the time when the subject signed informed consent until 30 days after the treatment administration.

If the Investigator detects a SAE in a study subject after the end of the period of observation (i.e., 30 days post treatment to 24 months) and considers the event related to prior study treatment or procedures, he or she should contact the Medical Monitor to determine how the AE should be documented and reported. An SAE form should be completed and sent to Medical Monitor.

Association of an event with the device can be excluded (at investigator discretion if deemed unrelated to treatment) if the event occurs later than the following latency period after the last product/device application:

- 30 days for non-serious adverse events,
- 30 days for SAEs
- 30 days for pregnancy, or 30 days if the subject initiates new anticancer therapy, whichever is earlier

If events occur after these latency periods, they will not be recorded, unless deemed associated (related) with the device treatment.

Any SAE brought to the attention of an investigator at any time outside of the time period specified above must be reported immediately to the Sponsor if the event is considered to be product/device related.

## 10.5 Documentation and Reporting of Adverse Events

Adverse events, SAEs, and other reportable safety events will be reported by the participant (or, when appropriate, by a caregiver, surrogate, or the participant's legally authorized representative).

The investigator, who is a qualified physician, and any designees are responsible for detecting, assessing, documenting, and reporting events that meet the definition of an AE or SAE as well as other reportable safety events. Investigators remain responsible for following up AE, SAEs and other reportable safety events for outcome.

All AEs (whether serious or non-serious) for the first 30 of the study must be documented in the eCRF. After 30 days, only AE's and SAE's deemed treatment associated will be collected.

The Investigator must document all AEs that occur during the first 30 days of the study on the respective pages provided in the eCRF in accordance with the instructions for the completion

of adverse event reports in clinical studies. These instructions are provided in the Investigator file and in the eCRF itself.

Every attempt should be made to describe all AEs in terms of a diagnosis. If a clear diagnosis has been made, individual signs and symptoms should not be recorded unless they represent atypical or extreme manifestations of the diagnosis, in which case they should be reported as separate events. If a clear diagnosis cannot be established, each sign and symptom must be recorded individually.

#### 10.5.1 Nature

The **nature** of the event will be described in precise, standard medical terminology (i.e. not necessarily the exact words used by the subject). If known, a specific diagnosis should be stated (e.g., flu like symptoms).

#### 10.5.2 Severity

The **severity** of the AE will be described in terms of Grades according to the CTCAE v.5.0 and according to the investigator's clinical judgment.

| Grade   |                                                                      | Definition                                                                                                                              |
|---------|----------------------------------------------------------------------|-----------------------------------------------------------------------------------------------------------------------------------------|
| Grade 1 | mild                                                                 | asymptomatic or mild symptoms; clinical or diagnostic observations only; intervention not indicated.                                    |
| Grade 2 | moderate                                                             | minimal, local or noninvasive intervention indicated; limiting age-appropriate instrumental activities of daily life (ADL)  |
| Grade 3 | severe or medically significant but not immediately life-threatening | hospitalization or prolongation of hospitalization indicated; disabling; limiting self-care ADL                             |
| Grade 4 | life-threatening consequences                                        | urgent intervention indicated                                                                                                           |
| Grade 5 | death related to AE                                                  | -                                                                                                                                       |

#### 10.5.3 Duration

The **duration** of the event will be described by the start date and end date.

For SAEs, the start date is the date on which the event became serious. The end date of an SAE is the date when the event resolved (not when serious criteria were no longer fulfilled).

#### 10.5.4 Relationship

Adverse events are also classified according to the degree of responsibility of the investigational device itself or of the procedure for implementation of a medical device in accordance with the following categories:

- **Not related:** relationship to the device or procedures can be excluded when:
  - the event has no temporal relationship with the use of the investigational device, or the procedures related to application of the investigational device;
  - the serious adverse event does not follow a known response pattern to the medical device (if the response pattern is previously known) and is biologically implausible;

- the discontinuation of medical device application or the reduction of the level of activation/exposure – when clinically feasible – and reintroduction of its use (or increase of the level of activation/exposure), do not impact on the serious adverse event;
- the event involves a body-site or an organ that cannot be affected by the device or procedure;
- the serious adverse event can be attributed to another cause (e.g. an underlying or concurrent illness/ clinical condition, an effect of another device, drug, treatment or other risk factors);
- the event does not depend on a false result given by the investigational device used for diagnosis, when applicable;

To establish the non-relatedness, not all the criteria listed above might be met at the same time, depending on the type of device/procedures and the serious adverse event.

- Possible: the relationship with the use of the investigational device or comparator, or the relationship with procedures, is weak but cannot be ruled out completely. Alternative causes are also possible (e.g., an underlying or concurrent illness/ clinical condition or/and an effect of another device, drug or treatment). Cases where relatedness cannot be assessed, or no information has been obtained should also be classified as possible
- Probable: the relationship with the use of the investigational device or comparator, or the relationship with procedures, seems relevant and/or the event cannot be reasonably explained by another cause.
- Causal relationship: the serious adverse event is associated with the investigational device, comparator or with procedures beyond reasonable doubt when:
  - the event is a known side effect of the product category the device belongs to or of similar devices and procedures;
  - the event has a temporal relationship with investigational device use/application or procedures;
  - the event involves a body-site or organ that
    - the investigational device or procedures are applied to;
    - the investigational device or procedures have an effect on;
  - the serious adverse event follows a known response pattern to the medical device (if the response pattern is previously known);
  - the discontinuation of medical device application (or reduction of the level of activation/exposure) and reintroduction of its use (or increase of the level of activation/exposure), impact on the serious adverse event (when clinically feasible);
  - other possible causes (e.g., an underlying or concurrent illness/ clinical condition or/and an effect of another device, drug or treatment) have been adequately ruled out;
  - harm to the subject is due to error in use;
  - the event depends on a false result given by the investigational device used for diagnosis, when applicable;

To establish the relatedness, not all the criteria listed above might be met at the same time, depending on the type of device/procedures and the serious adverse event.

### 10.5.5 Outcome

The **outcome** of the event will be described in terms of:

- Recovered: fully recovered or by medical or surgical treatment the condition has returned to the level observed at the first study related activity after the subject signed the informed consent

- Recovering: the condition is improving, and the subject is expected to recover from the event. This term should only be used when the subject has completed the study
- Recovered with sequelae: as a result of the AE, the subject suffered persistent and significant disability/incapacity (e.g., became blind, deaf, paralyzed). Any AE recovered with sequelae should be rated as an SAE
- Not recovered
- Fatal
- Unknown: This term should only be used in cases where the subject is lost to follow-up.

Insofar as possible all adverse events should be followed-up to determine the final outcome of the event. Details of follow-up should be recorded on the SAE report form, if applicable (e.g., discontinuation of study medication, if specific treatment is required, if hospitalization is required etc.).

## 10.6 Documentation and Reporting of Serious Adverse Events

If the AE is serious, the Investigator must complete in addition to the “Adverse Event” eCRF page a “SAE report form” (electronic copy can be downloaded and/printed from the eCRF) at the time the SAE is detected. This form must be sent immediately, i.e., within 24 hours upon becoming aware of the SAE to the Sponsor or delegate by e mail to:

[[contact]](mailto:[contact])

The initial report should be as complete as possible, including details of the current illness and (serious) AE, the reason why the event was considered serious, date of onset and stop date (if applicable), diagnostic procedures and treatment of the event, relevant medical history and concomitant medication and action taken with study medication.

Every attempt should be made to describe all AEs in terms of a diagnosis. If a clear diagnosis has been made, individual signs and symptoms should not be recorded unless they represent atypical or extreme manifestations of the diagnosis, in which case they should be reported as separate events. If a clear diagnosis cannot be established, each sign and symptom must be recorded individually.

For the time period beginning at treatment allocation through 90 days following cessation of treatment, or 30 days following cessation of treatment if the subject initiates new anticancer therapy, whichever is earlier, any SAE, or follow up to a SAE, including death due to any cause other than progression of the cancer under study, whether or not related to the Sponsor's product, must be reported.

Any SAE brought to the attention of an investigator at any time outside of the time period specified above must be reported immediately to the Sponsor if the event is considered to be treatment related.

## **10.7 Reporting of Pregnancy and Lactation to the Sponsor**

Although pregnancy and lactation are not considered adverse events, it is the responsibility of investigators or their designees to report any pregnancy or lactation in a subject (spontaneously reported to them) that occurs during the first 30 days of the study.

Pregnancies that occur after the consent form is signed but before treatment with Rhenium-SCT must be reported by the investigator if they cause the subject to be excluded from the study.

Pregnancies that occur from the time of treatment through 30 days following treatment, must be reported by the investigator.

### **Follow-up of Missing Information**

Information not available at the time of the initial report (e.g., an end date for the AE or laboratory values received after the report) must be documented on a "Serious Adverse Event" form, with the box "Follow-up" checked under "Report type".

All subjects who have an AE, whether considered associated with the use of the investigational products or not, must be monitored to determine the outcome. The clinical course of the AE will be followed up according to accepted standards of medical practice, even after the end of the period of observation, until a satisfactory explanation is found, or the Investigator considers it medically justifiable to terminate follow-up.

Should the AE result in death, a full pathologist's report should be supplied, if possible.

The sponsor will identify missing information for each SAE report. Requests for follow up will be sent to the site monitor for further processing. The site monitor will follow up information in regular intervals from the Investigators until all queries are resolved or no further information can be reasonably expected. All responses to queries and supply of additional information by the Investigator should follow the same reporting route and timelines as the initial report.

## **10.8 Deaths**

In the case of a subject dying, the investigator will document the cause of death in the Death CRF page. If possible, a death certificate should be obtained with the cause of death evaluated and documented.

## **10.9 Expedited Reporting of Adverse Events**

### **10.9.1 Development Safety Update Reports**

The sponsor or sponsor representative will prepare and submit development update safety reports (DSURs) for Rhenium-SCT to IRB/IECs as required.

### **10.9.2 Medical Device Vigilance Reporting**

The sponsor evaluates in close collaboration with the investigator, whether the serious adverse event requires vigilance reporting or documentation only according to the applicable

regulations (MDR 2017/745 Art. 87). Vigilance reporting is necessary when the serious incident or field safety corrective action (FSCA) involving device made available on the market.

The sponsor or its representative will take responsibility for notifying (serious) incidents and FSCA immediately to the Competent Authority and the Ethics Committee as applicable per local regulations and timelines.

The sponsor is responsible for reporting periodic safety update reports (PSUR), trend reports, premature termination or suspension of the clinical trial, and the final Study Report to Regulatory Authorities, Ethic Committees and investigators as applicable per local regulations and timelines.

## 11. STATISTICAL METHODS

### 11.1 Determination of Sample Size

The primary objective of the study is to estimate CR rate and show non-inferiority to historical values for CR rate following surgery and or radiotherapy. Complete response rate for BCC is 91% at 5 years and for SCC 79%. Review of the published papers for brachytherapy shows the split between BCC and SCC is 2:1, 1.68:1 and 2.1:1.

Based on previous studies, the CR rate for BCC and SCC is expected to be close to 100% following Rhenium-188 SCT treatment. For simplicity, assuming 1 lesion per subject, a sample size of 120 subjects is sufficient to provide at least 80% power to conclude non-inferiority using a one-sided alpha of 0.025 under the following circumstances (Table 3).

**Table 3. Sample size calculation**

| Non-inferiority margin | Assumed CR rate |
|------------------------|-----------------|
| 85%                    | ≥94%            |
| 86%                    | ≥94%            |
| 87%                    | ≥95%            |
| 88%                    | ≥96%            |
| 89%                    | ≥97%            |
| 90%                    | ≥97%            |

CR: complete response

Note. A series of simulations (1000) were run to explore the potential impact of different ratios of BCC:SCC on the estimated overall, historical CR rate, assuming the SCC rate was 79% and the BCC rate 91%.

For ratios between 1.5:1 (BCC: SCC) to 3.5:1, the range of median (from simulation) overall CR rate was 87% to 89%. Accordingly, the table above is applicable irrespective of the BCC:SCC ratio.

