**Table 1. Sample size calculation**

| Non-inferiority margin | Assumed CR rate |
|-------------------------------|------------------------|
| 85%                           | ≥94%                   |
| 86%                           | ≥94%                   |
| 87%                           | ≥95%                   |
| 88%                           | ≥96%                   |
| 89%                           | ≥97%                   |
| 90%                           | ≥97%                   |

CR: Complete response

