#### **Efficacy analysis:**

Primary efficacy endpoint: Complete Response (CR).

The number of lesions treated per subject will be summarised.

The number (and percentage) of lesions in each category (CR, PR, SD and progressive PD) at each timepoint (6 months, 12 months and 24 months) and the overall best response will be presented. The percentage of lesions achieving CR during the study (i.e., CR being the best overall response) will be estimated and presented with exact 95% confidence limits overall and by tumour type.

Secondary efficacy endpoints: Change from baseline in QoL, comfort of treatment, and cosmetic outcomes.

The QoL questionnaire will be scored according to the author's instructions. Change from baseline in score will be calculated. Descriptive statistics will be presented for actual score and change from baseline by timepoint, and overall and by tumour type (BCC/SCC). A mixed model will be fitted with change from baseline as the outcome variable. Baseline score will be included as a covariate and timepoint (6 months/12 months) tumour type, tumour stage as factors. Other relevant prognostic factors assessed at baseline will be included. From the model the adjusted mean change at each timepoint will be obtained and presented with 95% confidence limits. Adjusted mean change will be estimated overall and by tumour type.

Comfort with treatment is being assessed using a questionnaire. The frequency (and percentage) of subjects reporting each option for each question will be presented.

Cosmetic outcome (subject and clinician rated) is being assessed at 12 months and 24 months using a visual analogue score (VAS). Descriptive statistics will be presented overall and by tumour type (BCC or SCC). A mixed model will be fitted with VAS as the outcome variable. Tumour type and tumour stage will be included as factors. Other relevant prognostic factors assessed at baseline will be included. From the model the adjusted mean score will be obtained and presented with 95% confidence limits. Adjusted mean score will be estimated overall and by tumour type.

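### Non-inferiority is a primary aim in Section 11.1, but six CR thresholds from 85% to 90% are listed and none is chosen, and which one is relevant depends on the BCC:SCC mix

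*Protocol*

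**What the plan says.** Section 11.1 gives the primary objective as to estimate the CR rate and to "show non-inferiority to historical values for CR rate following surgery and or radiotherapy". The benchmark comes from two historical rates, 91% for BCC and 79% for SCC, and three published BCC:SCC splits are cited: 2:1, 1.68:1 and 2.1:1.

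The sizing statement is that, "assuming 1 lesion per subject, a sample size of 120 subjects is sufficient" to give "at least 80% power to conclude non-inferiority" "using a one-sided alpha of 0.025" in six situations. Table 3 (repeated as Table 1 in the synopsis) lists them. The column headed "Non-inferiority margin" holds 85%, 86%, 87%, 88%, 89% and 90%, paired with assumed CR rates of 94%, 94%, 95%, 96%, 97% and 97%.

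The note to Table 3 says that for ratios from 1.5:1 to 3.5:1 "the range of median (from simulation) overall CR rate was 87% to 89" per cent, and concludes: "Accordingly, the table above is applicable irrespective of the BCC:SCC ratio".

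For the primary analysis, Section 11.7 and the synopsis say that the percentage of lesions with CR "will be estimated and presented with exact 95% confidence limits overall and by tumour type". No value is named with which to compare those limits.

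**The concern.** A stated alpha and power belong to a test against one null value. Here six are offered and none is adopted, so the protocol does not say what result would count as non-inferior. The entries are also not margins. A margin is the loss against the benchmark that one is willing to accept; these are absolute CR rates. What margin each implies depends on the benchmark, and the benchmark depends on the tumour mix. A row at or above the benchmark allows no loss at all and is in effect a superiority test.

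At stake is the main efficacy claim. A result in the low to mid 90s could be reported as non-inferior or not, according to the row used. The study is open label (Section 8.1.8) and response is judged by the site investigator (Appendix 5), so response data can be visible while the threshold is still unset.

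**Working it through.** **Inputs.** n=120, one lesion per subject, one-sided alpha 0.025, six thresholds p0 with paired assumed rates (Section 11.1, Table 3); historical rates 91% and 79% and ratios 1.5:1 to 3.5:1 (note to Table 3); exact limits (Section 11.7).

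**1. Reproduce Table 3.** With an exact binomial test, the pass mark r is the smallest count with P(X ≥ r | n=120, p0) ≤ 0.025. Power is P(X ≥ r) at the assumed rate. This is the same rule as requiring the lower exact two-sided 95% limit to exceed p0.

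| Threshold | Pass mark of 120 | Observed CR | Power at the table's assumed rate | Power at true CR 94% |
|---|---|---|---|---|
| 85% | 110 | 91.7% | 89.3% (94%) | 89.3% |
| 86% | 111 | 92.5% | 81.6% (94%) | 81.6% |
| 87% | 112 | 93.3% | 85.3% (95%) | 70.6% |
| 88% | 113 | 94.2% | 89.1% (96%) | 56.8% |
| 89% | 114 | 95.0% | 93.0% (97%) | 41.5% |
| 90% | 115 | 95.8% | 84.7% (97%) | 26.8% |

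All six rows reach 80%, and lowering any assumed rate by one point takes that row below 80%. The table is sound row by row.

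**2. What the missing choice is worth.** A count of 110 to 114 passes at least the 85% row and fails at least the 90% row. P(110 ≤ X ≤ 114) with n=120:

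| True CR | 94% | 95% | 96% | 97% | 98% |
|---|---|---|---|---|---|
| Probability | 63% | 52% | 34% | 15% | 3% |

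**3. The benchmark by mix.** For a BCC:SCC ratio of k:1 the historical rate is (k × 91 + 79)/(k + 1).

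- 1.5:1: (136.5 + 79)/2.5 = 86.2%
- 1.68:1: (152.88 + 79)/2.68 = 86.5%
- 2:1: (182 + 79)/3 = 87.0%
- 2.1:1: (191.1 + 79)/3.1 = 87.1%
- 3.5:1: (318.5 + 79)/4.5 = 88.3%

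**4. What each row then means.** The 89% and 90% rows lie above the benchmark at every ratio listed. At mixes up to 2:1 the 87% and 88% rows also leave no positive margin (87.0 − 87 = 0 and 87.0 − 88 = −1.0 at 2:1). The 85% row allows a loss of 86.2 − 85 = 1.2 points at 1.5:1 and 88.3 − 85 = 3.3 points at 3.5:1. If the benchmark itself were the threshold, the pass mark would be 111 of 120 at 1.5:1, 112 at 2:1 and 113 at 3.5:1.

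**5. The stated 87% to 89%.** The weighted means run from 86.2% to 88.3%, which is 0.8 and 0.7 points lower. The note reports medians of 1000 simulations in whole per cents, and the simulated sample size is not given. Repeating sets of 1000 shows how far discreteness and rounding can go. At N=200 the low end rounded to 87% in about half of sets and the high end to 89% in about 95% or more. At N=120 the high end reached 89% in under 1% of sets. At N=1000 the results were 86% and, in at least 99.5% of sets, 88%.

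**The case against.** The strongest reply is that the gap is one of wording. Each row is a properly powered exact test. Two-sided exact 95% limits correspond to one-sided 0.025, so only the comparator is missing. Sections 5.1 and 5.2 frame the primary objective and endpoint as estimation, which Section 11.7 delivers. Section 11.2 announces a statistical analysis plan, which may fix the threshold. The protocol also expects CR close to 100%, where all six rows agree.

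Part of this stands. At a true CR of 98% the ambiguous zone has only a 3% chance. But Table 3 itself works with assumed rates from 94%, where the chance is 63%. And Section 11.1 does not leave the test to a later document: it states a non-inferiority aim, an alpha and a power, and ties them to six alternatives.

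On the note, a fair reading is that the 85% to 90% grid covers the benchmark over plausible mixes. That is true, also with 86.2% to 88.3%. It does not make the table independent of mix, because the mix decides which row is relevant.

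Four stronger inferences are tempting, and the documents do not support them:

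- That most rows sit at or above the benchmark. This is so for four of six up to 2:1, but for three at 2.1:1 and two at 3.5:1.
- That 87% to 89% is a calculation error. Simulated medians and rounding could produce it.
- That the sample size is wrong. It reproduces.
- That the threshold will be picked after the data are seen. The analysis plan is not at hand, and the interim analysis (Section 11.10) concerns patient-reported outcomes and foresees no amendments.

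**Conclusion.** The concern holds as a badly fixed decision threshold. The protocol claims a non-inferiority test with stated error rates but gives six null values, called margins, without choosing among them. The pass mark spans 110 to 115 of 120, and at a true CR of 94% the power spans 89% to 27%. Two of the six rows are superiority tests at every stated ratio, and the statement that the mix is irrelevant does not follow from the protocol's own rates.

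These figures assume 120 independent lesions, one per subject as in Section 11.1, the exact binomial rule, and 91% and 79% taken as given. The difference between 87–89% and the weighted means is under one point and is a matter for clarification only.

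**What to change.** Before any CR data are reviewed, put one rule in Sections 11.1 and 11.7: non-inferiority is concluded if the lower exact two-sided 95% limit for CR exceeds a single fixed threshold. Set it below the benchmark at the expected mix, and state the implied margin in percentage points. At 2:1, for example, only the 85% and 86% rows qualify, with margins of 2.0 and 1.0 points.

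A fixed number is preferable to one computed from the mix actually enrolled, which cannot be matched to a row in advance.

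Keep only the chosen row of Tables 1 and 3 with its power, and relabel the column as CR threshold. Delete the claim that the table applies whatever the ratio. Give the weighted benchmark (86.2% to 88.3%) beside the simulated range, or state the simulated sample size.

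This costs wording only, with no extra subjects or visits. The sponsor gives up choosing the threshold later.
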